## Abstract

**Background:**

Atherosclerotic cardiovascular disease (ASCVD) remains a major source of mortality in China. Convincing evidence has demonstrated that the reduction of low-density lipoprotein cholesterol (LDL-C) is correlated with lowering ASCVD risk. The efficacy of lifestyle management in lipid levels reduction has been confirmed in numerous studies. However, considering that low compliance to lifestyle management has limited the benefits of lowering lipid levels, cognitive behavior therapy (CBT) is proposed as a solution to improve clinical outcomes. The objective of this trial is to compare the LDL-C outcome in ASCVD patients receiving mobile device-based CBT to a control group, with both groups under standard pharmacological treatments.

**Methods:**

This trial is designed as a multicenter, prospective randomized controlled trial with a 6-month follow-up. Mean LDL-C level and the percentage of different LDL-C levels, coefficient of variation of LDL, General Self-Efficacy Scale (GSEs), quality of life index (QL-index), etc., between the two groups at baseline, 1, 3, and 6 months will be measured.

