### Sample size {14}

Considering the primary outcome variable as the reduction in the mean LDL-C from baseline to week 24, an absolute reduction of 20% in LDL-C is expected [22, 23]. One hundred twenty-two subjects per group was calculated initially to offer 80% power at a one-sided 0.05 significance level according to a 1:1 ratio of random grouping. Allowing for a maximum follow-up loss rate of 20% in both groups, 300 patients were determined as the target sample size—150 patients in each group.

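### One secondary responder outcome requires HDL above 500 mg/dL, so as written it will be 0% in both arms and cannot show an effect

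*Protocol article*

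**What the plan says.** The abstract (Methods) lists, among the quantities to be compared between the groups, "the percentage of different LDL-C levels". It gives no cut-off and does not mention HDL.

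The section Secondary outcome measures gives the cut-offs. Its eight items include two percentages of participants:

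- LDL below 70 mg/dL, alone;
- LDL below 70 mg/dL combined with HDL above 500 mg/dL.

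Both thresholds of the composite are printed in mg/dL in the same line. HDL appears in no other outcome, and no other section gives a second HDL value.

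The primary endpoint (Primary outcome measure) is the mean change in LDL-C from randomization to week 24. The planned size (Sample size {14}) is stated thus: "Allowing for a maximum follow-up loss rate of 20% in both groups, 300 patients were determined as the target sample size", that is 150 per group.

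**The concern.** The HDL threshold decides who counts as a responder on the composite. A cut-off of 500 mg/dL is about seven times the LDL threshold it is paired with (500/70 = 7.1), and HDL cholesterol ordinarily lies in the tens of mg/dL. Applied literally, nobody qualifies in either arm, and the outcome carries no information about the intervention.

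This is the only listed outcome that uses HDL, so the trial would lose its one stated measure of joint LDL and HDL control. There is a second risk. The trial is open-label, and authorized investigators may evaluate data while it runs (Plans for assessment and collection of outcomes {18a}). If a workable cut-off were chosen late and without a documented source, nobody could show that the choice was independent of the results.

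**Working it through.** **Nothing to reproduce.** The figure in question is a typed threshold, not a calculated one. The sample size calculation concerns LDL-C only ("an absolute reduction of 20% in LDL-C is expected") and does not involve HDL. It supplies only the number of patients used below.

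**Inputs**

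- Cut-off c = 500 mg/dL (Secondary outcome measures).
- N = 300 patients, 150 per group (Sample size {14}).
- HDL distribution: *assumption*, since the article gives none. Mean m from 40 to 70 mg/dL and SD s from 10 to 25 mg/dL, taken in every combination. A log-normal shape is used because its upper tail is heavier than that of a normal distribution with the same mean and SD, which favours the plan.

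**Formulas**

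- σ = √ln(1 + (s/m)²) and μ = ln(m) − σ²/2
- z = (ln 500 − μ)/σ, with ln 500 = 6.2146
- Expected number above 500 mg/dL = 300 × P(Z > z)

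**Worst corner of the range (m = 40, s = 25)**

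- σ = √ln(1 + 0.625²) = 0.574
- μ = 3.689 − 0.165 = 3.524
- z = (6.2146 − 3.524)/0.574 = 4.69
- P(Z > z) = 1.4 × 10⁻⁶, so 300 × P = 0.0004

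**Other combinations**

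| Mean | SD | Expected number above 500 mg/dL among 300 |
|---|---|---|
| 40 | 20 | 3.5 × 10⁻⁶ |
| 50 | 15 | 2.0 × 10⁻¹³ |
| 50 | 25 | 4.8 × 10⁻⁵ |
| 60 | 20 | 3.2 × 10⁻⁹ |
| 60 | 25 | 5.7 × 10⁻⁶ |
| 70 | 25 | 7.5 × 10⁻⁷ |
| 60 | 30 (outside the range, deliberately wide) | 0.0003 |

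The maximum over the assumed range is thus about 0.0004. In that worst corner the probability that none of the 300 exceeds the cut-off at a given visit is still 0.9996. Over the four assessment times (baseline, 1, 3 and 6 months) the expected number of exceedances is at most 4 × 0.0004 = 0.0016. The LDL condition can only lower these counts.

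**What a test would show.** With no responders in either arm, the expected responder cells of the two-by-two table are zero and the chi-squared statistic is undefined. Fisher's exact test returns p = 1. A t-statistic on the responder indicator is 0/0. The power to detect any effect of CBT on this outcome is nil.

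**The case against.** The strongest reply is that this is an obvious typing or unit error in a condensed article. The full protocol and the data-capture system, which are not shown, may hold a sensible value. Zero responders in every patient would expose the slip at once, so a misleading report of no effect is unlikely. Restoring a documented value would be an erratum, not a change of endpoint.

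Most of that stands, and it limits the weight of the point. It does not make the published definition usable. An explicit wrong number is not a detail that an article leaves to a fuller document, and the intended value cannot be recovered from the text.

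Three stronger readings are tempting but not supported:

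- *That the LDL-C percentage outcome announced in the abstract is itself compromised.* The abstract phrase has no HDL term and no error. Linking it to the composite is an inference, and it fits the LDL-only outcome, which is fully usable.
- *That the intended cut-off is one tenth of the printed one.* A factor-of-ten slip is a plausible guess, but nothing in the article confirms it.
- *That any correction would now be post hoc.* This is so only if no earlier record of the intended value exists and the cut-off is chosen after the data are seen.

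**Conclusion.** The composite outcome is wrong as written, and the impact is minor. The expected number of patients above the HDL cut-off is at most about 0.0004 among 300, so the outcome will in practice be 0 of 150 against 0 of 150 and cannot be tested.

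This rests on an assumed HDL distribution (mean 40 to 70 mg/dL, SD 10 to 25 mg/dL, log-normal), because the article supplies none. The conclusion is the same at every point of that range and for the wider case of mean 60 and SD 30. The damage is confined to one secondary outcome. The primary endpoint, the sample size, the LDL below 70 mg/dL outcome and the remaining secondary outcomes do not use HDL.

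**What to change.** Before the analysis, look up the HDL cut-off in the full protocol or the trial registration, correct it in Secondary outcome measures, and record the correction with its date and source. Check that the analysis programs and any derived variable in the data-capture system use the same value.

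If no intended value is documented, drop the composite and keep LDL below 70 mg/dL as the responder outcome. A cut-off should not be guessed or chosen after the data are seen.

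The cost is one number and a dated note. No further patients, visits or measurements are needed.

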**Discussion:**

This trial should demonstrate that the implementation of mobile-based CBT intervention will be potentially effective in lowering LDL-C levels in ASCVD patients.

**Trial registration:**

Chinese Clinical Trial Registry (ChiCTR2100046775) [registered: 2021/5/28].

## Administrative information

Note: The numbers in curly brackets in this protocol refer to SPIRIT checklist item numbers. The order of the items has been modified to group similar items. (see http://www.equator-network.org/reporting-guidelines/spirit-2727-statement-defining-standard-protocol-items-for-clinical-trials/).

## Introduction

### Background and rationale {6a}

Atherosclerotic cardiovascular disease (ASCVD) prevalence has been persistently increasing these years. In addition, ASCVD remains the leading cause of mortality in Chinese populations [1]. Over the past few decades, major risk factors of ASCVD have been confirmed, including the increased level of low-density lipoprotein cholesterol (LDL-C) [2]. The accumulation of LDL-C in the arterial wall can induce an inflammatory response. This leads to plaque formation and finally results in ASCVD due to plaque rupture and thrombosis. Numerous studies have consistently demonstrated that prolonged reduction of LDL-C is remarkably correlated with lowering ASCVD risk [3]. As a result, several guidelines have recommended evidence-based lipid-lowering treatments, based on lifestyle interventions, as the main components of preventing ASCVD events [3–6]. However, the issue of lower compliance to pharmacological and non-pharmacological treatments has limited the benefits of lowering lipid levels [7–9], with an estimation that 9% of ASCVD events have resulted from poor compliance [3]. In consequence, it is necessary to improve patient compliance, and furthermore, to improve the clinical outcome.

Cognitive behavior therapy (CBT) is a psychological therapy developed by A.T. Beck in the 1960s, which aims to modify out-of-control emotions, behavior, and cognition through goal-directed and systematic procedures [10]. CBT emphasizes the improvement of self-efficacy through cognitive and behavioral changes, which will benefit the patients in clinical outcomes as a result [11]. Recently, CBT has been suggested as a potential treatment to control cardiovascular disease risk factors such as weight, blood pressure, and blood glucose. Previous studies have shown that CBT can significantly reduce patients’ body weight and waist circumference [12], improve blood glucose control [13], and reduce the number of drugs required for blood pressure control [14]. Although these studies have revealed the efficacy of CBT in designated patient populations, most of the interventions are conventional methods delivered with oral communications given by healthcare providers. Study data of mobile device-based CBT used in ASCVD patients is limited. With the increasing availability and accessibility of mobile device-based healthcare, the advantage of assigned sessions, comprehensible structure, and cognitive orientation makes internet-delivered CBT a potential solution to impact a large population at a relatively low cost.

CBT-based lifestyle interventions have the potential to provide more effective patient education, leading to healthier habits at a population level. Considering these underlying factors, we assume mobile-based CBT lifestyle interventions are potentially effective in reducing LDL-C levels in ASCVD patients.

### Evidence before this study

Lifestyle modification is an evidence-based strategy associated with better clinical outcomes in ASCVD patients, accomplished with improved self-efficacy and risk factor control. Conventional lifestyle intervention is performed in an outpatient setting where healthcare providers can communicate with patients face-to-face. However, limited accessibility has been an obstacle for ASCVD patients to receive a consistent intervention. Novel delivery methods including mobile-based interventions have been developed to promote healthy lifestyles. We searched PubMed, Medline, and Embase for researches that had investigated the use of CBT in cardiovascular patients from October 2016 to October 2021. Search terms included cognitive behavioral therapy, mobile-based, cardiovascular disease, stroke, coronary syndrome, and dyslipidemia. MeSH (Medical Subject Headings) were used to include synonyms. Based on our review, we found that mobile-based CBT has been applied to improve psychological conditions in CVD patients, but few articles had investigated its improvement in objective parameters, such as lipid panels, to evaluate clinical outcomes. We identified a systemic review and meta-analysis of seventeen clinical trials (*n* = 5780) that had investigated blood pressure in patients receiving digital health interventions. The results prove that digital health interventions are effective in lowering blood pressure in hypertensive populations [15]. There is another systemic review and meta-analysis identified (56 studies; 263 effect sizes; *n* = 4060) that had investigated objective data to evaluate the improvement in immune system with psychological interventions. According to the study, psychological interventions including CBT therapy can effectively control the level of C-reactive protein in the body and slow down the progress of heart disease and Alzheimer’s disease. Among various psychological interventions, CBT is identified as superior to other psychotherapy in strengthening the immune system [16].

### Added-value of this study

CBT is widely applied to treat psychological conditions, which are mostly measured by subjective data. We identified some researches that had investigated blood pressure, C-reactive protein, etc., but there is limited information on CBT’s potential effect on lipid levels. To the best of our knowledge, this study will be the first study that evaluates CBT’s potential efficacy of reducing LDL-C levels in ASCVD patients. Moreover, this study provides a treatment that is patient-centered. Up to 50% of individuals who were involved in psychological interventions did not maximally benefit from the interventions [17]. Based on the previous studies, we consider the lack of patient-specificity is potentially limiting the efficacy. Therefore, the analysis and customization regarding specific populations are of great significance to improve the treatment selection and outcome of patients. We propose this novel treatment strategy in ASCVD patients based on the HAPA model [11]. It treats ASCVD management as a long-term process requiring patients’ self-efficacy. Customized CBT integrates mindfulness mediation, cognitive training, etc., with blood lipid management to improve self-efficacy. If the results are positive, these findings should demonstrate that the clinical improvement of mobile-based CBT intervention will be measurable as objective findings.

### Objectives {7}

Aim 1: To determine the efficacy of mobile-based CBT interventions, compared with conventional interventions, in ASCVD patients receiving standard treatments;Hypothesis 1a (primary study hypothesis): a significant reduction in objective parameters, including LDL-C level, will be demonstrated in participants randomly assigned to the CBT group relative to participants in the conventional interventions group.

Aim 2: To improve our capacity to match patients to treatments more efficiently by identifying self-efficacy, and quality of life.Hypothesis 2a: a significant improvement in self-efficacy, and quality of life, measured by scales and questionnaires, will be demonstrated in participants randomly assigned to the CBT group relative to participants in the conventional interventions group.

### Trial design {8}

This study is a multicenter, prospective, randomized, controlled, open-label parallel-group superiority trial. Patients will be randomly allocated at a 1:1 ratio to evaluate the efficacy of CBT to lower blood lipids in ASCVD patients. The study protocol follows the Standard Protocol Items: Recommendations for Interventional Trials (SPIRIT) [18].

## Methods: participants, interventions, and outcomes

### Study setting {9}

The study will be performed at Sir Run Run Shaw Hospital Affiliated to Zhejiang University, Hangzhou, Zhejiang, China, in conjunction with investigators at Ningbo Ninth Hospital, Ningbo, China, Zhejiang Xinhua Hospital, Zhejiang, China, Lin’an People’s Hospital, Zhejiang, China, and YuHang Fifth People’s Hospital, Zhejiang, China.

### Eligibility criteria {10}

#### Inclusion criteria

Patients’ inclusion criteria will be (1) age from 18 to 80 years old; (2) meet of ASCVD diagnostic criteria, including the history of acute coronary syndrome (ACS), myocardial infarction (MI), stable or unstable angina, transient ischemic attack, surgical history of coronary or peripheral vascular reconstructions, etc.; (3) currently taking statins by prescription; (4) no difficulty in using smartphones, basic Chinese reading and writing skills, basic calculation skills; and (5) acceptance of the terms and conditions of the study and signature of the informed consent form.

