#### Exclusion criteria

Patients’ exclusion criteria will be (1) meet of very high-risk ASCVD diagnostic criteria (diagnostic criteria is determined according to 2020 Chinese expert consensus on lipid management of very high-risk atherosclerotic cardiovascular disease patients); (2) one or more of the following complications: heart failure, ventricular tachycardia, second to third-degree atrioventricular block, uncontrolled atrial tachycardia (including atrial flutter, atrial fibrillation, etc.), mural thrombus, cardiac aneurysm, dysfunction or rupture of papillary muscle, severe sinus bradycardia (heart rate < 50 beats/minute), sinus arrest, etc.; (3) history of cardiac arrest; (4) acute non-cardiogenic complications: such as infections, kidney failure, hyperthyroidism, etc.; (5) severe cardiovascular conditions: moderate to severe valvular stenosis, hypertrophic cardiomyopathy, other forms of ventricular outflow tract stenosis, acute myocarditis, pericarditis, active endocarditis, suspected or known aneurysm rupture, acute pulmonary embolism, or pulmonary infarction; and (6) vulnerable populations, including patients with mental disorders, critical illness, age < 18 years old, pregnancy, students or subordinate of principal investigators, employees of the research institute, etc. This trial does not exclude any other concurrent therapies or interventions.

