### Primary outcome measure

*LDL-C level*. The primary endpoint will be the mean change in LDL-C level [time Frame: from randomization (day 0) to V5 (week 24) for a total of 6 months of treatment]. Per guideline, the LDL-C level has been validated as a primary measurement for the clinical efficacy of the treatments [3].

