#### Concealment mechanism {16b}

Allocation concealment will be guaranteed through the following mechanism. Staff will log in to the EDC Trial Data cloud and enter the information for the participants. The EDC Trial Data system will randomly assign participants to either group in a 1:1 ratio. A patient profile will be generated after the necessary baseline information has been entered. Account number and password are required when assessing data.

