### Statistical methods

#### Statistical methods for primary and secondary outcomes {20a}

Categorical variables will be expressed in numerical values with their respective percentages and compared using the chi-squared test at baseline. Continuous variables will be expressed as mean ± SD and compared using the *t*-test. The significance of primary and secondary endpoints will be evaluated with the paired-samples *t*-test. A *p*-value < 0.05 indicates statistical significance. All data will be analyzed with the SPSS.

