#### Methods for additional analysis (e.g., subgroup analysis) {20b}

No additional analysis will be conducted.

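### The test fixed for the LDL-C below 70 mg/dL endpoint neither compares the arms nor adjusts for baseline LDL-C, although patients may enter already below 70

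*Protocol article*

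**What the plan says.** In the protocol article, the only lipid-related inclusion criterion is "currently taking statins by prescription". The nearest exclusion criterion is "meet of very high-risk ASCVD diagnostic criteria", which is a risk category with no LDL-C value attached. A patient below 70 mg/dL on statins is therefore eligible.

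The primary outcome is anchored to baseline: "The primary endpoint will be the mean change in LDL-C level". Among the secondary outcomes, the ratio of measured to baseline LDL is anchored too. The percentage below 70 mg/dL, and the composite that adds an HDL condition, are not.

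On analysis, section {20a} names the chi-squared test for categorical variables at baseline and a t-test for continuous variables. It then states: "The significance of primary and secondary endpoints will be evaluated with the paired-samples" t-test. It names no covariate. Section {16b} says "The EDC Trial Data system will randomly assign participants to either group in a 1:1 ratio", with no stratification by LDL-C. Section {20b}, on subgroup and similar analyses, says "No additional analysis will be conducted".

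**The concern.** A patient who starts below 70 mg/dL and is still below it at 6 months counts the same as one who was brought below it. Baseline LDL-C is therefore likely to be the strongest predictor of this endpoint that the trial collects, and the stated analysis does not use it.

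The stated test also does not answer the question. A paired test compares a patient's later value with the same patient's earlier one. Applied to a below-70 indicator, it describes movement within a group. It gives no estimate of the difference between CBT and control.

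At stake is the precision of one secondary comparison, and its sensitivity to the arms happening to differ in baseline LDL-C. The primary endpoint is a separate matter.

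**Working it through.** **Inputs.** From section {14}: 122 per arm, 80% power, one-sided 0.05, 20% loss, and "an absolute reduction of 20% in LDL-C is expected". The documents give no mean, SD, share below 70 or within-patient correlation for LDL-C. Those are assumed here: mean/SD of 80/25, 90/30 and 105/30 mg/dL, correlation ρ between baseline and 6 months of 0.5 or 0.7, normal distributions, and an effect equal to a downward shift by a percentage of the mean.

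**1. The plan's own figure.** The 122 per arm cannot be rebuilt without an SD. It implies a standardised effect of √2 × (1.645 + 0.842)/√122 = 0.318. For loss, 122/0.8 = 152.5, so 153 against the stated 150. Conversely 150 × 0.8 = 120, the number per arm used below. The figure concerns the primary endpoint, and this point does not depend on it.

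**2. Share already below 70 at entry.** Φ((70 − mean)/SD) gives Φ(−0.40) = 34%, Φ(−0.667) = 25% and Φ(−1.167) = 12% for the three settings.

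**3. How many stay below 70.** In the control arm this is Φ₂(z, z; ρ)/Φ(z), with z = (70 − mean)/SD. At 90/30 it is 60% for ρ = 0.7 and 48% for ρ = 0.5. Over all settings it runs from 35% to 66%. Since the control distribution is the same at both times, these are also the shares of control successes who began below 70.

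**4. Is the effect diluted?** At 90/30, ρ = 0.7 and a 10% effect, the success rate rises by about 14 points in patients starting below 70 and about 9 points in the rest. The weighted sum, 0.25 × 14 + 0.75 × 9, is about 10 points overall. Here the low-baseline patients raise the average difference. At mean 105 the contrast is 15–18 against 7–8 points, and at mean 80 it is 13 against 12. Only at mean 80 with a 20% effect does it reverse slightly (23–25 against 25–26).

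Dilution does appear if nearly all low-baseline patients are assumed to stay below 70 equally in both arms. The difference then shrinks by (1 − f), where f is the share starting below 70. With assumed rates of 20% and 35% in the others and f = 30%, 15 points become 0.7 × 15 = 10.5. Power at 122 per arm, two-sided 0.05, falls from 75% to 37%. Neither assumption comes from the documents.

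**5. Chance imbalance.** At 90/30 with 120 per arm, the standard error of the arm difference in the share starting below 70 is √(2 × 0.252 × 0.748/120) = 5.6 points. With ρ = 0.7, about 60% of low starters and (0.252 − 0.151)/0.748 = 13.5% of the others end below 70 without treatment. One standard error of imbalance therefore moves the endpoint by 5.6 × (0.60 − 0.135) = 2.6 points, against an expected difference of about 10.

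**6. Power with and without baseline.** Unadjusted chi-squared against logistic regression on arm and baseline LDL-C, 120 per arm, in two independent simulations:

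| Mean, ρ, effect | 600 trials | Gain | 1,000 trials | Gain |
|---|---|---|---|---|
| 80, 0.7, 10% | 48% → 64% | 16 | 52% → 67% | 15 |
| 90, 0.7, 10% | 39% → 54% | 15 | 44% → 60% | 16 |
| 90, 0.7, 15% | 74% → 88% | 14 | 76% → 89% | 13 |
| 90, 0.5, 10% | 41% → 48% | 7 | 45% → 50% | 5 |
| 105, 0.5, 15% | 80% → 84% | 4 | 80% → 86% | 6 |

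Simulation error is about √(0.25/600) = 2 points on each figure. Over all runs the gain is roughly 5 to 17 points. At the planned 20% effect the unadjusted test already has about 95% to 97% power, so little room is left: about 2 to 5 points.

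**7. Restricting to patients at or above 70 at baseline.** In the same model this generally loses power against the plain full comparison: about 66% against 77% (mean 90, ρ = 0.5, 15%) and 41% against 54% (mean 80, ρ = 0.5, 10%).

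**The case against.** Several counter-arguments have force.

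- **The percentage at target is a legitimate endpoint.** Keeping patients at target fits a trial whose rationale is compliance, and 1:1 randomisation prevents systematic bias. Both stand, and the endpoint need not be changed.
- **Baseline is partly handled.** The abstract's Methods say that the percentages at different LDL-C levels will be measured at baseline as well as at follow-up, so the starting share below 70 will be visible by arm. The change and ratio endpoints use baseline as well. This stands, but neither puts baseline LDL-C into the comparison on the threshold endpoint.
- **Covariates are commonly left to an SAP.** This stands in part. The sentence in {20b} sits under subgroup analysis and does not clearly bar a covariate in a main analysis. But {20a} does more than leave the matter open: it fixes a test, and that test does not fit the endpoint.
- **The gain is measured against a test the plan does not name.** True: chi-squared is named only at baseline. The power figures show what baseline adjustment adds to a sensible between-arm test. They do not measure the plan's own test, which makes no between-arm comparison of this outcome.

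A reader might infer that patients already below 70 necessarily dilute the effect, so that the trial should look mainly at those at or above 70. The documents do not support this. Whether dilution occurs depends on how many low-baseline patients stay below 70, which is not given, and under the normal model that group mostly gains more than the rest. The restricted comparison has the advantage only under the assumption that nearly all of them stay (59% against 37% power at f = 30%).

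**Conclusion.** The point holds in a limited form. Entry below 70 mg/dL is possible, the endpoint ignores baseline, and the test assigned to it neither compares the arms on a binary outcome nor uses baseline LDL-C as a predictor. The consequence is lost precision and exposure to chance imbalance on a secondary endpoint. Systematic bias does not follow, and dilution is not shown.

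The size rests on assumed normal distributions, means of 80 to 105 mg/dL, correlations of 0.5 to 0.7 and 120 patients per arm. On that basis adjustment is worth roughly 5 to 17 points of power if the LDL-C effect is 10% to 15%, and about 2 to 5 points if it is the planned 20%. Replacing the paired test matters whatever those values are.

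**What to change.** In section {20a}, replace the paired test for LDL-C below 70 mg/dL at 6 months with a between-arm regression, logistic or modified Poisson, on arm and continuous baseline LDL-C. Report the adjusted risk difference with its confidence interval. Specify the same for the LDL/HDL composite. Its printed HDL cut-off (500 mg/dL) should be confirmed first, because the model needs both outcomes to occur.

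The percentage reaching below 70 among patients at or above 70 at baseline may be shown by arm as description only, since under the normal model it has less power than the full comparison.

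Eligibility stays as it is, since recruitment is reported complete. The cost is wording: baseline LDL-C is already collected and no further patients or visits are needed. The change should be dated before outcome data are analysed by arm.
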